### Statistical analysis

#### Primary study endpoint

The primary study endpoint is the pathological tumor response per CMS using the TRG system according to Dworak [11]. Pathologic tumor regression rates with corresponding 95% confidence intervals will be analyzed per CMS subgroup using the Wilson Method.

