## Abstract

**Background:**

It is estimated that around 15–30% of patients with early stage colon cancer benefit from adjuvant chemotherapy. We are currently not capable of upfront selection of patients who benefit from chemotherapy, which indicates the need for additional predictive markers for response to chemotherapy.

It has been shown that the consensus molecular subtypes (CMSs), defined by RNA-profiling, have prognostic and/or predictive value. Due to postoperative timing of chemotherapy in current guidelines, tumor response to chemotherapy per CMS is not known, which makes the differentiation between the prognostic and predictive value impossible. Therefore, we propose to assess the tumor response per CMS in the neoadjuvant chemotherapy setting. This will provide us with clear data on the predictive value for chemotherapy response of the CMSs.

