In the proposed study we will investigate the predictive value of the CMS classification on chemotherapy response in a neoadjuvant setting, including pathological response and radiological response and their correlation with RFS and OS. This allows us to determine therapy efficacy in individual patients and per subtype.

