### Objective

The primary aim of this study is the evaluation of the pathological tumor response to neoadjuvant systemic chemotherapy per CMS in patients with MSS high risk stage II and stage III colon cancer.

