### Secondary study parameters/endpoints

Additional pathological markers to assess the tumor response: the modified Ryan scheme (TRS) [13] and expression of Ki-67 and Caspase-3 and morphological cytostatic-cytotoxic effects on HE-stained tissue slides.Pathological response per TRG and TRS category separately for the different CMS subtypes.Radiological tumor response to neoadjuvant chemotherapy.Recurrence free survival (RFS) at two and three years. RFS is defined as the time elapsed between the diagnosis of the primary tumour and either the date of any recurrence of disease, time of death, or the date of the last follow-up visit at which a patient was considered to have no recurrence.Overall survival (OS) at five and ten years.Therapy-induced CMS differences.Prognostic and predictive value of cytotoxic lymphocytes (CytoLym) and cancer-associated fibroblasts (CAF) infiltration scores.Diagnostic accuracy of ctDNA measurements for monitoring treatment response to neoadjuvant treatment and detection of residual disease.Exploration of proteome profiles for monitoring treatment response to neoadjuvant treatment and detection of residual disease.Percentages of pathological complete (R0), pathological microscopic incomplete (R1) and pathologically macroscopic incomplete (R2) resections.Surgical complication rate (i.e. wound infections and anastomotic leak).

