#### Secondary study endpoints

Categorical data (pathological tumor response according to the Modified Ryan scheme) are compared using Chi-square analysis or Fisher’s exact test and are shown as numbers, relative and absolute rates. Continuous data (CytoLym and CAF infiltration scores, radiological tumor response, pathological response by percentage of Ki-67 and Caspase-3 positive neoplastic cells) are compared using non-parametric T-test or Mann-Whitney U test where appropriate and are shown as mean and standard deviation or median and interquartile range (25–75%). *P*-values are two-tailed and results < 0.05 are considered significant.

The OS at 5 and 10 years and RFS at 2 and 3 years will be calculated and depicted by means of the Kaplan Meier technique and will be compared using the (stratified) logrank test. Hazard ratios and 95% confidence intervals will be calculated with a (stratified) cox-proportional hazard analysis. The RFS will be analyzed per CMS subgroup, per TRG and radiological response. All estimates will be accompanied by 95% confidence intervals.

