The proposed neoadjuvant approach requires reliable clinical TNM staging to minimize the risk of overtreating patients with stage I or low risk stage II colon cancer. A meta-analysis analyzing the accuracy of T and N staging on CT imaging showed that T1–2 can be reliably distinguished from T3–4 (sensitivity 96% and specificity 70%), while nodal involvement is unreliable with a pooled sensitivity and specificity of 78 and 68% respectively [18]. Therefore, only T stage will be used to select patients. Second, only patients with an MSS status will be included which will be determined on the biopsies, following the latest recommendations of the update of the ESMO guideline to refrain from adjuvant chemotherapy in high-risk stage II MSI colon cancer patients as the possible clinical benefit is too low [19]. This was also seen in the FOxTROT trial, where MSI status was associated with a significantly higher rate of poor/no response (96% vs. 66%, *p* < 0.0001) [20]. Using the proposed selection of patients with a MSS cT3–4NxM0 colon tumor, up to 26% of patients is estimated to be overtreated [21, 22].

Results from this study, in which we analyze both the pathological and radiological tumor response per CMS, will lead to improved patient stratification and clearer insight into which patients benefit from chemotherapy. This will allow us to identify the group of patients that receives chemotherapy appropriately and the group of patients that may not benefit from the current treatment regimen. Future studies should focus on whether chemotherapy can be withheld in this patient group or on the development of new therapies to improve patient outcome.

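### The primary Dworak response has no between-subtype contrast, although the trial is presented as investigating whether CMS predicts response

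*Protocol article*

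**What the plan says.** All places are in the protocol article.

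- **Objective:** "The primary aim of this study is the evaluation of the pathological tumor response to neoadjuvant systemic chemotherapy per CMS". This is descriptive wording.
- **Statistical analysis, Primary study endpoint:** "Pathologic tumor regression rates with corresponding 95% confidence intervals will be analyzed per CMS subgroup using the Wilson Method". No difference, test or significance level is attached to the primary endpoint.
- **Sample size calculation:** precision within each subtype, with a maximum margin of error of 15%. It plans 209 evaluable patients (CMS2 49%, CMS3 17%, CMS4 35%) and margins of 8.9, 14.7 and 10.3%. It assumes response no higher than about 30% in any subtype, and warns that the margins grow if rates are nearer 50%.
- **Secondary study endpoints (analysis):** "Categorical data (pathological tumor response according to the Modified Ryan scheme) are compared using Chi-square analysis or Fisher’s exact test". The groups compared are not named, and the Dworak grade is not listed.
- **Secondary study parameters/endpoints:** "Pathological response per TRG and TRS category separately for the different CMS subtypes".
- **Abstract, Background:** "This will provide us with clear data on the predictive value for chemotherapy response of the CMSs". The Abstract's Discussion also speaks of analysing predictive value, with a view to later studies of withholding chemotherapy in a particular subtype.
- **Background, closing paragraph:** "we will investigate the predictive value of the CMS classification on chemotherapy response in a neoadjuvant setting".
- **Discussion, last paragraph:** "This will allow us to identify the group of patients that receives chemotherapy appropriately and the group of patients that may not benefit".

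**The concern.** If all subtypes responded equally, CMS would carry no information about response. Predictive value in the sense used here is therefore largely a matter of differences in response rate between subtypes. The primary analysis yields three separate rates and no estimate of how far apart they are.

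Two things are at stake. First, readers who want to know whether subtypes differ will tend to compare the three intervals by eye, and that misses differences a direct contrast would show. Second, a contrast computed later from the reported counts would be post hoc: the pairs, the scale and the handling of multiplicity would be chosen with the data in view. A comparison on the modified Ryan score beside an uncompared Dworak response would also leave unclear which of the two answers the question.

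**Working it through.** **Inputs.** From Sample size calculation: 209 evaluable patients, shares 49/17/35%, CMS3 n = 35 with 11 responders, ceiling about 30%. Subtype sizes: 0.49 × 209 ≈ 102, CMS3 = 35, 0.35 × 209 ≈ 73. (These sum to 210 because the printed shares sum to 101%.) The documents give no target difference, so the 15% and 10% rates below are assumptions.

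**1. The plan's own margins.** The Wilson interval is centred at (p + z²/2n)/(1 + z²/n) with half-width z√[p(1−p)/n + z²/4n²]/(1 + z²/n), z = 1.96.

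| Subtype | Responders/n | Rate | 95% interval | Half-width |
|---|---|---|---|---|
| CMS2 | 32/102 | 31.4% | 23.2 to 40.9% | 8.9 |
| CMS3 | 11/35 | 31.4% | 18.6 to 48.0% | 14.7 |
| CMS4 | 22/73 | 30.1% | 20.8 to 41.4% | 10.3 |

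These match the stated 8.9, 14.7 and 10.3%. As an estimation study the design is consistent.

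**2. Precision of a difference at the same sizes.** With Wilson limits l and u, the Newcombe interval for p₁ − p₂ runs from d − √[(p₁−l₁)² + (u₂−p₂)²] to d + √[(u₁−p₁)² + (p₂−l₂)²].

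For CMS2 v CMS4:
- lower arm √[(0.3137−0.2318)² + (0.4144−0.3014)²] = 0.140
- upper arm √[(0.4091−0.3137)² + (0.3014−0.2082)²] = 0.133
- half-width (0.140 + 0.133)/2 ≈ 13.6 points

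The same steps give 17.2 points for CMS2 v CMS3 and 18.1 for CMS3 v CMS4. The simple formula 1.96√[0.3 × 0.7 × (1/n₁ + 1/n₂)] gives 13.8, 17.6 and 18.5.

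**3. Separate intervals against a direct contrast.** Exact enumeration over all outcomes of two independent binomials, CMS2 n = 102 and CMS4 n = 73. Each column is the probability of declaring a difference.

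| True rates (CMS2 v CMS4) | Pooled score test | Newcombe interval excludes 0 | Wilson intervals do not overlap |
|---|---|---|---|
| 30% v 15% | 65% | 65% | 32% |
| 30% v 10% | 92% | 92% | 70% |
| 30% v 30% | 5% | 5% | 0.6% |

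The last row shows the cause: non-overlap of two 95% intervals is far stricter than a 5% test.

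**4. One possible result.** With 31/102 (30.4%, 22.3 to 39.9%) and 11/73 (15.1%, 8.6 to 25.0%) the intervals overlap. Yet by the formula in step 2 the difference is 15.3 points, 95% interval 2.5 to 26.8.

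**5. What a global test can do.** Power of the 2-df chi-square test at 102/35/73, from the noncentral chi-square with λ = Σnᵢ(pᵢ − p̄)²/[p̄(1 − p̄)]: 27% for CMS2/3/4 rates of 30/30/20%, 57% for 30/30/15%, and 84% for 30/30/10%. If pairwise differences were shown only after a significant global test, 100 − 27 = 73% of trials at 30/30/20% would report none.

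**The case against.** The strongest reply is that the primary design is coherent: aim, endpoint, analysis and sample size are all stated per subtype, and the margins reproduce. That stands. The mismatch is only with the broader statements in the Abstract, Background and Discussion.

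Several stronger readings are tempting, and the documents do not support them.

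- *The article states a conclusion that CMS predicts response.* It states an aim and an expectation, and leaves to future studies whether chemotherapy can be withheld.
- *The planned analysis cannot inform predictive value at all.* A very low response rate in one subtype is itself informative and its interval addresses that directly. Separate intervals can also reveal a large difference (70% probability at 30% v 10%).
- *Overlap of intervals is the plan's decision rule.* No such rule appears. Step 3 measures an informal reading that the plan invites, and anyone with the counts can compute a difference.
- *Response is never compared between subtypes.* The secondary endpoint list, which names TRG and TRS by subtype, read with the chi-square or Fisher sentence, plausibly implies a comparison between subtypes. It remains secondary, and for the Dworak grade it is not explicit.
- *A 40% v 20% scenario.* It shows a similar gap (82% for the score test v 54% for non-overlap), but 40% exceeds the ceiling on which the plan is sized.

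It is also fair to say that a condensed article may leave supportive contrasts to a fuller document. But the article does fix the primary method and does name tests for secondary endpoints, so the contrast that bears on its headline question is the conspicuous one to lack. If a fuller document already names it, the article's wording is all that needs aligning.

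**Conclusion.** The point holds as a should-fix. The primary analysis and sample size serve the descriptive aim, but no between-subtype contrast of the Dworak good/poor response is specified, while the trial is presented as investigating predictive value. Within the plan's ceiling of about 30%, relying on separate intervals for CMS2 v CMS4 roughly halves the chance of seeing a 15-point difference (32% against 65%) and cuts it from 92% to 70% for a 20-point one.

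The figures assume the planned evaluable numbers and subtype shares, unadjusted two-sided 5% comparisons, and illustrative true rates. It is not a must-fix: no data are lost, the difference can be recovered from planned data, and the primary aim as worded is answered. Nor does the fix make the trial well powered. At 30/30/20% the global test has only 27% power, so the main gain is a prespecified estimate with honest precision.

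**What to change.** 1. In Statistical analysis, Primary study endpoint, keep the Wilson intervals per subtype. Add the three pairwise differences in Dworak good-response rate (CMS2, CMS3, CMS4) with Newcombe-Wilson 95% intervals, reported whatever the result of any test.
2. Add one global 2-df test of good v poor response across the three subtypes. If pairwise significance is to be claimed, make pairwise tests only after a significant global test; with three groups this holds the family-wise error at 5%. State that this controls the tests and does not give the unadjusted intervals simultaneous coverage.
3. In Sample size calculation, state the expected half-widths of the differences beside the existing margins: about 14 points (CMS2–CMS4), 17 (CMS2–CMS3) and 18 (CMS3–CMS4).
4. In the Secondary study endpoints analysis, name the groups compared for the modified Ryan score.
5. Limit predictive-value statements to what these contrasts show.

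The cost is a few sentences, with no new data or patients, but the change must be made before the response data are analysed. The downside is that half-widths of 14 to 18 points look less favourable than the per-subtype margins of 8.9 to 14.7.

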#### Secondary study endpoints

Categorical data (pathological tumor response according to the Modified Ryan scheme) are compared using Chi-square analysis or Fisher’s exact test and are shown as numbers, relative and absolute rates. Continuous data (CytoLym and CAF infiltration scores, radiological tumor response, pathological response by percentage of Ki-67 and Caspase-3 positive neoplastic cells) are compared using non-parametric T-test or Mann-Whitney U test where appropriate and are shown as mean and standard deviation or median and interquartile range (25–75%). *P*-values are two-tailed and results < 0.05 are considered significant.

The OS at 5 and 10 years and RFS at 2 and 3 years will be calculated and depicted by means of the Kaplan Meier technique and will be compared using the (stratified) logrank test. Hazard ratios and 95% confidence intervals will be calculated with a (stratified) cox-proportional hazard analysis. The RFS will be analyzed per CMS subgroup, per TRG and radiological response. All estimates will be accompanied by 95% confidence intervals.

#### Sample size calculation

We based our sample size calculation on the desired precision with which we will be able to estimate the pathological response rates to neoadjuvant chemotherapy within each CMS subtype. This precision is quantified by the margin of error (the radius of the 95% confidence interval), which we set at a maximum of 15%. This margin of error is achieved with 35 patients in the least prevalent CMS subgroup, namely CMS3, and an anticipated 11 pathologic responses, yielding a response rate of 31% with a 95%CI of 19–48%. Based on the currently observed ratios of subtypes derived from the large consensus dataset after exclusion of the MSI tumors (which holds CMS1 tumors for most part) we will need a total of 209 MSS patients (CMS2 49%, CMS3 17%, CMS4 35%). With this sample size we anticipate maximum margins of error of 8.9, 14.7, and 10.3% for CMS2, CMS3, and CMS4 respectively, and 6.2% overall.

The above depends on the assumption that the response rates will not be higher than ~ 30% within each CMS subgroup. If response rates will actually be closer to 50%, the maximum margin of error will increase.

The sample size hence indicates that for the analysis, 209 patients will be needed for whom follow-up and subtype is known. We expect a 25% loss in patients due to loss of follow-up, insufficient quality of the biopsy material or failure to faithfully assign patients to a subgroup based on the RNA expression profiles resulting in a total of 262 patients needed to have sufficient data for both the primary and secondary outcomes.

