**Methods:**

In this prospective, single arm, multicenter intervention study, 262 patients with resectable microsatellite stable cT3–4NxM0 colon cancer will be treated with two courses of neoadjuvant and two courses of adjuvant capecitabine and oxaliplatin. The primary endpoint is the pathological tumor response to neoadjuvant chemotherapy per CMS. Secondary endpoints are radiological tumor response, the prognostic value of these responses for recurrence free survival and overall survival and the differences in CMS classification of the same tumor before and after neoadjuvant chemotherapy. The study is scheduled to be performed in 8–10 Dutch hospitals. The first patient was included in February 2020.

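### The 25% loss allowance was added to 209 (209 × 1.25 = 262) instead of taken from enrolment (209 / 0.75 = 279), so 262 covers only about a 20% loss

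*Protocol article*

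**What the plan says.** The sample size rests on precision within each consensus molecular subtype. In the protocol article, Sample size calculation, the criterion is "the margin of error (the radius of the 95% confidence interval), which we set at a maximum of 15"%. The rarest subtype drives the number: "This margin of error is achieved with 35 patients in the least prevalent CMS subgroup, namely CMS3, and an anticipated 11 pathologic responses". The plan puts the corresponding CMS3 estimate at 31%, with an interval from 19 to 48%. With subtype shares of 49% (CMS2), 17% (CMS3) and 35% (CMS4), the plan requires 209 patients for the analysis, defined as patients whose follow-up and subtype are both known. For that number "we anticipate maximum margins of error of 8.9, 14.7, and 10.3% for CMS2, CMS3, and CMS4 respectively". The margin for all subtypes together is put at 6.2%. The precision is conditional on response rates of no more than about 30% in each subtype.

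The loss allowance follows: "We expect a 25% loss in patients due to loss of follow-up, insufficient quality of the biopsy material". Failed subtype assignment is named as a further cause, and the paragraph ends with the enrolment figure, "resulting in a total of 262 patients needed to have sufficient data for both the primary and secondary outcomes". The Abstract (Methods) repeats the total: "262 patients with resectable microsatellite stable cT3–4NxM0 colon cancer". The interval method is given under Primary study endpoint, where regression rates "will be analyzed per CMS subgroup using the Wilson Method".

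**The concern.** The 209 is the number that must remain after losses, and the losses listed (follow-up, biopsy quality, subtype assignment) happen to patients already enrolled. The 25% should therefore come off the enrolled number. A total of 262 looks like 209 plus a quarter of 209, which is too small for the loss the plan itself expects.

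At stake is whether the enrolment figure delivers the analysable number and the CMS3 count on which the precision statement is built. CMS3 has the least room, because its planned margin of 14.7% lies only 0.3 points below the 15% maximum.

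**Working it through.** **Inputs**, all from the protocol article: 209 analysable patients, 25% loss, 262 enrolled, shares 49/17/35%, 11 responses in 35 CMS3 patients, a response ceiling of about 30%, a 15% maximum margin (Sample size calculation), and Wilson 95% intervals (Primary study endpoint).

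**1. Reproduce the enrolment total.**
- Allowance added to the analysable number: 209 × 1.25 = 261.25, rounded up to 262. This matches.
- Allowance taken from enrolment: 209 / (1 − 0.25) = 278.7, rounded up to 279. This does not match and is 17 more than 262.

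**2. What 262 delivers.**
- With a 25% loss: 262 × 0.75 = 196.5, so about 196 analysable, 12 to 13 short of 209.
- Loss at which 209 remain: 1 − 209/262 = 53/262 = 20.2%.
- CMS3 expected in 196.5: 33.4 at a share of 17%, or 32.9 at 35/209. That is about 33, against 35.
- CMS2: 196.5 × 0.49 = 96.3. CMS4: 196.5 × 0.35 = 68.8.

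**3. Reproduce the plan's margins at 209.** The Wilson half-width is h = z·√(p(1−p)/n + z²/(4n²)) / (1 + z²/n), with z = 1.96.
- CMS3, 11/35: √(0.006157 + 0.000784) = 0.08332, divided by 1.1098, gives h = 14.7%. The interval is 18.6 to 48.0%, as stated.
- Overall, n = 209: 6.2% at 30% or 31%, as stated.
- CMS2, n = 102: 8.8% at 30% or 31% and 8.9% at 11/35. CMS4, n = 73: 10.3% at 30%. These agree with the stated 8.9 and 10.3%, although not at one common response rate.

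**4. The same formula at about 196 analysable patients.**

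| Group | n | Stated for 209 | At 30% | At 31% |
|---|---|---|---|---|
| CMS2 | 96 | 8.9% | 9.0% | 9.1% |
| CMS3 | 33 | 14.7% | 14.9% | 15.1% |
| CMS4 | 69 | 10.3% | 10.6% | 10.7% |
| Overall | 196 | 6.2% | 6.4% | 6.4% |

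Worked example, CMS3 with n = 33:
- At 30%: √(0.006364 + 0.000882) = 0.08512, divided by 1.1164, gives 14.94%.
- At 31%: √(0.006482 + 0.000882) = 0.08581, divided by 1.1164, gives 15.07%.
- At whole counts, 10/33 gives 14.98% and 11/33 gives 15.3%.
- The smallest CMS3 count with a half-width of 15% or less is 33 at a 30% rate and 34 at 31%.

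**The case against.** Four points can be made for the plan.

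- **The 25% could mean 25% of 209.** Then 262 is consistent. But the text speaks of a loss in patients from causes that act on enrolled patients, and 53 of 262 is a 20% loss. On this reading the stated percentage still misleads.
- **Not every loss touches the primary endpoint.** Pathological response is read on the resection specimen, so a resected and subtyped patient who is later lost to follow-up still counts. If at least 25 − 20.2 = 4.8 of the 25 percentage points are such late losses, the primary endpoint keeps its 209. The documents do not give the split, so this is possible but unproven. It does not remove the shortfall in the set that the plan defines, which needs both follow-up and subtype and to which a single 25% is applied.
- **The printed margins are correct for what they describe.** They are tied to 209 and reproduce there. A reader might infer that every quoted margin is wrong. The documents do not support that: the fault lies in the step from 209 to 262.
- **The 15% criterion is not clearly breached.** A reader might infer from the lower CMS3 count that the plan misses its own maximum. At the plan's ceiling of about 30%, 33 patients give 14.94%, and 10/33 gives 14.98%. Only at 31% or slightly above does the half-width pass 15%, and then by about 0.1 point.

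It is also fair to say that this is an estimation design with no test or power claim resting on the number, and that the plan already warns of wider margins if response rates are nearer 50%.

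**Conclusion.** The enrolment figure is wrong as written. Under the plan's own 25% loss, 262 enrolled patients give about 196 analysable and about 33 CMS3 patients, not 209 and 35. For 209 to remain, either enrolment would be 279 or the loss would have to be about 20%.

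The consequence for precision is modest: each margin widens by about 0.1 to 0.4 percentage points over the printed value. The CMS3 margin moves from 14.7% to between 14.9% and 15.1%, so the reserve is spent and the target sits on the boundary. Which side it falls on depends on whether the plan's 30% or its 31% is used.

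This rests on three assumptions: the 25% is a share of enrolled patients, all of it reduces the set with follow-up and subtype known, and the subtypes occur in the planned proportions.

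**What to change.** Correct the loss sentence in Sample size calculation in one of two ways, keeping 262 there and in the Abstract:

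1. State that 262 covers a loss of about 20% of enrolled patients, if that rate is considered realistic. The 209, the 35 and the printed margins then stand.
2. Keep the 25% and state that it leaves about 196 analysable patients (about 96, 33 and 68 to 69 in CMS2, CMS3 and CMS4). Give the margins at one response rate: about 9.0, 14.9, 10.6 and 6.4% overall at 30%, or 9.1, 15.1, 10.7 and 6.4% at 31%. If 31% is used, the 15% maximum has to be reworded to the figure expected.

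It would help to say in either case how much of the allowance is later follow-up loss that leaves the pathological endpoint intact. Both routes cost only wording, and the second also slightly less favourable figures. Neither needs more patients. Holding both 209 and a 25% loss would mean 279 enrolled, 17 more.
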